#### Intervention group

From the first week of clinical activity, the intervention group performs video laryngoscopy with a hyperangulated blade as the standard method for every ETI. They are supervised by a board-certified anesthetist during each induction of general anesthesia. Following the completion of 200 ETI procedures by each resident within their randomized group (VL), the evaluation was concluded. For each ETI, residents indicated whether the following difficulties were present. Furthermore, the residents were asked to indicate whether any of the following complications had occurred in the case of each ETI. In addition, the rate of complications in both groups will be monitored by the study team.

#### Control group

The participants in the control group performed conventional direct laryngoscopy (HEINE Optotechnik Standard LED laryngoscope with a Macintosh blade, Gilching/Germany) from the first week of their clinical activity. They are also supervised by a board-certified anesthetist during each induction of anesthesia. Following the completion of 200 ETI procedures by each operator within their randomized group (DL), the evaluation was concluded.

### Criteria for discontinuing or modifying allocated interventions {11b}

Study participants may withdraw from the study at any time and without providing a reason, irrespective of their current stage in the study process. This includes scenarios such as the termination of their employment or relocation to another hospital. As a university hospital, we benefit from attracting staff with a strong interest in academic and scientific endeavors, which serves as a motivating factor for study participation. To ensure continuous support, a member of the study team is readily available to address any questions or concerns raised by participating residents. If, for whatever reason, the participants no longer wish to participate in the study, there will be no negative consequences. Likewise, no financial or other incentives will be given to participate in the study.

### Strategies to improve adherence to interventions {11c}

Our department has appointed academic staff to supervise the residents during their training. Research staff will encourage participants continue daily documentation.

### Relevant concomitant care permitted or prohibited during the trial {11d}

No concomitant treatments are excluded or prohibited as part of the study. This also applies to surgical procedures, medical treatments, or other forms of therapy administered to the patient. However, the study has no influence on these concomitant treatments. Of course, this information will be documented (e.g., type of operation).

### Provisions for post-trial care {30}

The project is covered by the business liability insurance of Heidelberg University, Faculty of Medicine Heidelberg, Germany.

### Outcomes {12}

Study participants will independently document various parameters on the case report form (CRF) immediately after tracheal intubation or, at the latest, shortly thereafter. Any complications arising during the procedure will be recorded no later than after extubation. This approach ensures that the documentation is provided in a timely manner and is directly related to the case.

#### Primary outcome measure

Successful tracheal intubation on the first attempt (Table 1).

#### Secondary outcome measure

Complications such as oxygen desaturation below SpO_2_ 90%, regurgitation, and dental or soft tissue trauma.Number of attempts made during laryngoscopy.The level of training with intubation success.Any failures or transitions to other rescue techniques.The use of OELM techniques such as BURP, CP, or adjustment of the participant's head and neck position.When using VL, record the occurrence of fogging and assess the glottic view using the Cormack-Lehane classification and the Percentage of Glottic Opening Score.Indications of difficult airway management (e.g., Mallampati Score, limited mouth opening)

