### Trial design {8}

The JuniorDoc-VL study is a randomized, controlled, patient-blinded trial of novice anesthesiology residents (< 1 month) trained in conventional DL and VL. The study design is illustrated in Fig. 1. The participating residents (*n* = 30) are randomly assigned 1:1 to either the DL group (control group) or the VL group (intervention group). Residents are allocated to one of the two groups once at the start of their clinical work in anesthesiology. This signifies that the overall study can be evaluated on the basis of 6.000 ETIs, which represents a significant sample size. The principal aim of this trial is to demonstrate that the experimental treatment (VL) is superior to the control (DL).

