## Assignment of interventions: allocation

### Sequence generation {16a}

At the beginning of the study, each resident is randomly assigned to either the intervention group (VL group) or the control group (DL group) in a 1:1 allocation. Each resident then performs all tracheal intubations within their assigned group. This approach ensures that the decision to randomize is made only at the outset of the study, with no switching between groups thereafter. This implies that each participant is immediately aware of their assigned study group following the enrolment phase and throughout the entirety of the study. The study employs Randomizer AT, a randomization software developed by the Medical University of Graz Institute for Medical Informatics, Statistics, and Documentation (IMI). Therefore, factors such as gender distribution cannot be influenced.

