### Analysis of the secondary outcomes

Complications will be analyzed with Kaplan-Meier curves and the log-rank test. The comparison of the view of the glottis will be analyzed using the Wilcoxon rank-sum test. Logistic regression and Cox regression will be used to explore the effect of additional explanatory variables.

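### As written, glottic view is recorded under video laryngoscopy only, yet the planned rank-sum comparison of the view needs values from the direct laryngoscopy arm too

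*Protocol article*

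**What the plan says.** Under *Secondary outcome measure*, the protocol article has one item on laryngoscopic view: "When using VL, record the occurrence of fogging and assess the glottic view using the Cormack-Lehane classification", with the POGO score added in the same sentence. *Analysis of the secondary outcomes* then states: "The comparison of the view of the glottis will be analyzed using the Wilcoxon rank-sum test". It names neither the groups compared nor the unit of analysis.

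The devices are fixed by arm. *Intervention group*: "the intervention group performs video laryngoscopy with a hyperangulated blade as the standard method for every ETI". *Control group*: "The participants in the control group performed conventional direct laryngoscopy", with a Macintosh blade. *Sequence generation {16a}* adds: "Each resident then performs all tracheal intubations within their assigned group", and rules out later switching. Changes of technique appear only as a secondary outcome, "Any failures or transitions to other rescue techniques", and the technique changed to is not named.

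**The concern.** The opening condition of the outcome item governs both of its verbs, so the view is tied to VL in the same way as fogging. A rank-sum test needs two independent samples. If residents complete the form as the outcome item reads, one of the two samples is never collected, and no later analysis plan can recover it.

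What is at stake is one planned secondary comparison. It bears on interpretation, because the Background and Discussion give better visualisation of the glottis as an advantage of VL. Without DL values, the trial could not show whether its own residents obtained a better view with VL than with DL.

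**Working it through.** The main check sets the sections of the protocol article side by side; the arithmetic only gives the size.

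**1. Is there another provision for a DL view?**
- *Secondary outcome measure*: the only mention of Cormack-Lehane or POGO as an outcome is the item conditional on VL. The separate item on indicators of a difficult airway gives pre-intubation signs as examples and does not name the view.
- *Table 1*, to which *Plans for assessment and collection of outcomes {18a}* refers for data collection, defines first-pass success, desaturation and hypotension only.
- *Intervention description {11a}* has residents record attempts and techniques. *Outcomes {12}* speaks of various parameters without listing the view.

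None of these provides for the view under DL.

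**2. What does the planned test need?** The trial has two arms, VL and DL, so a two-sample rank-sum test of the view most naturally compares these. It needs a view for both.

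**3. Size.** Inputs: 30 residents allocated 1:1 (*Trial design {8}*), 15 per arm (*Sample size {14}*), 200 intubations per resident (*Intervention group*, *Control group*).
- Total: 30 x 200 = 6,000, which reproduces the figure in *Trial design*.
- DL arm: 15 x 200 = 3,000, or 3,000 / 6,000 = 50% of all planned intubations.

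The 3,000 is the number of DL intubations for which the text makes no provision. It is not an estimate of how many values are missing.

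**4. Could a change of technique supply DL-arm views?** Only if VL were used as the rescue technique, which the article does not state. As an illustration on that assumption:
- *Sample size* assumes 80% first-pass success under DL, so 3,000 x (1 - 0.80) = 600 first attempts fail.
- If every one of these went to VL (an assumed upper bound), 3,000 - 600 = 2,400 intubations (80%) would still have no view.
- If 1%, 5% or 10% of DL-arm intubations were converted (assumed range), 30, 150 or 300 views would exist, leaving 99%, 95% or 90% without one.

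Any such views would be selected for failed DL, and would be VL views rather than DL views.

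**5. Does the missing-data rule help?** *{20c}* restricts evaluation to complete data. For this variable, that leaves no DL-arm values or only the selected ones.

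**The case against.** The strongest reply is that the sentence is loosely drafted. Fogging is a camera problem, so the VL condition may have been meant for fogging alone. The outcome item does not forbid assessing the view under DL, and the fact that a comparison is planned suggests that the authors expect views in both arms. The case report form would settle this, and it is not shown. *Intervention group* also refers to a list of difficulties recorded at each intubation, which the article does not reproduce. All of this stands as a limit on the point: a form with a Cormack-Lehane field for every case would reduce the correction to one sentence. It does not remove the point, because the published recording rule and the published analysis still disagree, and residents complete the forms themselves.

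Three stronger readings are tempting, and the document supports none of them.
- A reader might infer that DL views are in fact absent. The text shows only that nothing provides for them; the word *only* is an inference from the wording.
- A reader might infer that whatever control values exist all come from failed DL rescued with VL. No section says that VL is the rescue technique. After two failed attempts, the consultant takes over or instructs, with no device named.
- A reader might infer that the rank-sum test is to be run on individual intubations, ignoring residents. The analysis section states no unit, and the primary comparison is sized on 15 against 15 residents.

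It is also fair to say that the objective concerns first-pass success and that the abstract names only complications as the secondary endpoint.

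**Conclusion.** The point holds as an inconsistency between a stated recording rule and a stated analysis. Read literally, the outcome item provides for glottic view under VL only, while the analysis section plans a two-sample comparison of it. The arm without provision has 3,000 planned intubations, half of the total, so as written the comparison has no proper control sample and cannot be validly run.

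This rests on two readings: that the VL condition covers the view as well as fogging, as the grammar has it, and that the comparison is VL against DL, as the two-arm design implies. If the test was instead meant within VL, its groups are undefined and the sentence still needs correcting. It cannot be told from the article how many DL views have actually been lost. The outcome is secondary and the primary analysis is untouched. The point should be corrected, but it does not threaten the trial's main conclusion.

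**What to change.** Reword the outcome item, for example: *for the first laryngoscopy of every ETI in both arms, record the Cormack-Lehane grade (and POGO where assessable); record fogging only when VL is used.* Check that the case report form has the field for DL cases.

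In the analysis section, name the comparison as VL against DL by randomised arm and state the unit. Residents are randomised and each contributes 200 intubations, so use one summary per resident (to which a rank-sum test can still be applied, 15 against 15) or a model with a resident effect.

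If DL views have not been collected so far, report how many are missing. Then either restrict the comparison to the period in which both arms recorded the view, taking account of each intubation's place in the resident's sequence so that early VL cases are not set against later DL cases, or describe the view within VL only and drop the two-sample test.

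Cost: one or two extra entries per DL case and two edited sentences. The real loss is that views not recorded in DL cases since recruitment opened on April 15, 2024 cannot be recovered. Recruitment is planned to run to Dec 31, 2027, so a correction still protects later cases.

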#### Subgroups

Demographics: patients (age, gender, body mass index (BMI))American Society of Anesthesiologists (ASA) class.Analysis of care providers (clinical experience, training status, and experience in direct and indirect laryngoscopy)Type of procedure (e.g., general surgery, bariatric surgery).

#### Definition of the important outcome variables

Table 1 lists the most important outcome variables and their definitions.

### Participant timeline {13}

Residents will be approached during their first week of employment and invited to participate in the study. The study will continue until a total of 200 tracheal intubations have been performed, with an anticipated duration of approximately 1 year. The schedule of enrolment, interventions, and assessments are shown schematically in Fig. 2.

**Fig. 2 Fig2:**
[figure not shown]
The table shows in accordance with the SPIRIT Guidelines, the timetable, and schedule for the study participants

### Sample size {14}

The calculation of the sample size was based on achieving successful tracheal intubation on the first attempt and on organizational aspects and realistic feasibility. In recent trials, the VL demonstrated a first-attempt success rate of 92–97% in a mixed resident population. The study’s power was determined by assuming an 80% first-pass success rate in the DL group [1] and 92–94% in the VL group [16, 18]. This study was chosen for the sample size calculation because the aim was to compare VL and DL in first-year anesthesia residents in the operating room. Based on the current first-pass success rate, we hypothesized that a 10% increase in the VL group compared to the DL group would constitute a significant improvement in advanced airway management. To detect a difference in means of 10, with sample sizes of 15 in Group 1 (VL) and 15 in Group 2 (DL), the power is 0.66262. The power was computed using PASS 2024, version 24.0.2 NCSS, LLC. Kaysville, UT, USA.

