## Statistical methods

### Statistical methods for primary and secondary outcomes {20a}

A parallel two-group design will be used to test whether the Group 1 mean is different from the Group 2 mean (H0: μ1 − μ2 = 0 versus H1: μ1 − μ2 ≠ 0). The comparison will be made using a two-sided, two-sample equal-variance t-test, with a Type I error rate (α) of 0.05. The common standard deviation for both groups is assumed to be 10. The distribution of the data of the primary endpoint (FPS) is tested for normality using the Shapiro-Wilk test. In addition, graphical methods such as histograms and Q-Q plots are used to visually assess the distribution of the data. To compare FPS values between groups, either the parametric t-test (for normally distributed data) or the non-parametric Mann-Whitney U-test (for non-normally distributed data) is used, depending on the distribution. The choice of test was made based on the results of the normality test. Multiple logistic regression analysis of subgroup factors will allow us to assess the factors affecting FPS when comparing DL with VL, such as age, sex, ASA, BMI and provider experience. Cox regression can be used to evaluate the combined impact of the method and other explanatory variables. We used the following software for the calculation PASS 2024 Power Analysis and Sample Size Software (2024). NCSS, LLC. Kaysville, Utah, USA.

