## Discussion

This protocol outlines the methodology of the JuniorDoc-VL study, a randomized controlled trial designed to directly compare first-pass success (FPS), learning curves, and complications associated with DL vs. VL among first-year anesthesiology residents. Recent literature increasingly supports the potential benefits of routine video laryngoscopy use. One of the key advantages of VL is its ability to facilitate shared visualization of the glottic region, which can be particularly beneficial for teaching and training purposes [12, 19]. Evidence suggests that the learning curve for non-anesthetists is steeper with VL compared to DL [20]. A study conducted at our clinic, published in 2012, reported a first-pass success (FPS) rate of 85% for residents performing direct laryngoscopy after completing approximately 150 tracheal intubations [1]. In various medical departments, non-anesthetists are also involved in advanced airway management. However, they often do not achieve the high number of endotracheal intubations (ETIs) typically associated with skill acquisition in this area. This highlights the need for recommendations on how to address this situation and whether training in VL could be advantageous, given its steeper learning curve. Additionally, VL appears to minimize head and neck manipulation, which is particularly relevant for patients with suspected cervical spine injuries. The use of VL has been associated with a reduction in failed ETIs and lower complication rates, including decreased bleeding and dental trauma [15, 21, 22]. However, as with any other medical intervention, VL can also have disadvantages. For example, a meta-analysis has shown that the use of VL can affect the time to tracheal intubation despite improved visualization of the glottic region [23]. One of the most important aspects of VL is the type of blade used.

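### The sample-size section derives power from rates 12–14 points apart but reports it for 10 points, and the printed 0.66262 fits neither

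*Protocol article*

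**What the plan says.** The section Sample size {14} gives three statements of the effect, in this order.

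- Rates: "The study’s power was determined by assuming an 80% first-pass success rate in the DL group [1] and 92–94% in the VL group [16, 18". Just before this, a wider VL range is cited as background: "In recent trials, the VL demonstrated a first-attempt success rate of 92–97% in a mixed resident population".
- Target: "we hypothesized that a 10% increase in the VL group compared to the DL group would constitute a significant improvement". Whether the 10% is absolute or relative is not said.
- Calculation: "To detect a difference in means of 10, with sample sizes of 15 in Group 1 (VL) and 15 in Group 2 (DL"), with a printed power of 0.66262.

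The remaining inputs are in Statistical methods for primary and secondary outcomes {20a}: a "two-sided, two-sample equal-variance t-test, with a Type I error rate (α) of 0.05", and a common standard deviation of 10.

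The Discussion returns to the source of the 80% control rate, saying that it "reported a first-pass success (FPS) rate of 85% for residents performing direct laryngoscopy after completing approximately 150 tracheal intubations [1".

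**The concern.** A single power figure can rest on only one difference. The text names 80% against 92–94% as the assumptions from which power was determined, then gives the power for a smaller difference. If the rates were the basis, the difference should be 12 to 14. If 10 was the basis, the sentence about the rates is wrong. The printed power should at least settle which was used, but it agrees with neither.

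With 30 residents and a sample size that rests partly on feasibility, readers will use this section to judge what the trial could have detected, above all if the result is not significant. As printed, they cannot tell which effect the trial was planned to detect or how likely it was to detect it.

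**Working it through.** **Inputs.** n = 15 per arm, difference 10, and rates of 80% and 92–94% (Sample size {14}); two-sided equal-variance t-test, alpha 0.05, SD 10 (Statistical methods {20a}).

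**Differences implied by the rates.** 92 − 80 = 12 and 94 − 80 = 14. Neither is 10.

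**Formula.** Degrees of freedom = 15 + 15 − 2 = 28. The critical value is t(0.975, 28) = 2.048. The standard error of the difference is 10 × √(2/15) = 3.651. The noncentrality parameter is the difference divided by 3.651. Power is the probability that a noncentral t variable with 28 degrees of freedom falls outside ±2.048.

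**The protocol's own figure first.** For a difference of 10, the noncentrality parameter is 10 / 3.651 = 2.739 and power is 0.753. The normal approximation gives 0.782. The printed value is 0.66262, about 9 percentage points lower, so it does not reproduce.

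**Other differences, same inputs.**

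| Difference (points) | Noncentrality | Power |
|---|---|---|
| 8 (10% relative to 80%) | 2.191 | 0.562 |
| 9 | 2.465 | 0.66262 |
| 10 (stated) | 2.739 | 0.753 |
| 12 (92 − 80) | 3.286 | 0.887 |
| 14 (94 − 80) | 3.834 | 0.959 |

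**Working back from 0.66262.** At SD 10 it requires a difference of 9.00. At a difference of 10 it requires an SD of 11.11. The two are the same calculation, since 9/10 = 10/11.11 = 0.90.

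**Variants tried at a difference of 10 and SD 10.** One-sided test: 0.848. Two-sided alpha 0.025: 0.646. Mann-Whitney efficiency factors of 0.955, 0.864 and 0.667: 0.73, 0.69 and 0.56. Between 11 and 16 residents per arm, 12 gives 0.649 and 13 gives 0.687. None returns 0.66262.

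The section therefore carries three differences: 12–14 from the rates, 10 from the wording, and 9 from the printed power if SD 10 was used.

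**The case against.** The best defence is that 10 points is a deliberate target. The sentence on a 10% increase reads naturally as a smallest worthwhile improvement, with 80% and 92–94% as expected rates in the background. Planning for 10 when 12 to 14 is expected would be conservative. This is plausible, and it limits the harm. It does not rescue the text, which says outright that power was determined from those rates, and it does not explain 0.66262, which is not the power for 10 points at SD 10.

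It is also fair that the sample size rests partly on feasibility, that the article openly prints a power below conventional levels, and that a null result would be read mainly from its confidence interval. These points bear on how serious the error is, not on whether it exists.

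Three stronger readings are tempting and should not be drawn.

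- A reader might infer that the Discussion's 85% contradicts the 80%, since both cite the same source. It does not. The 85% was reached after about 150 intubations, and on a rising learning curve a mean of 80% over intubations 1 to 200 is compatible with it. The 85% is never used for sizing, so power figures built on it as the control rate are not the plan's own. That 94 − 85 also equals 9 is conjecture.
- A reader might infer that the assumed gain mixes device with operator experience. The description of a mixed resident population is attached to the 92–97% range, not expressly to the sources of the 92–94%. Who intubated in those sources cannot be established from the article.
- A reader might infer that the trial is more weakly powered than the article admits. On the stated inputs the reverse holds: 0.753 for 10 points exceeds the printed 0.66262.

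**Conclusion.** The section is wrong as written, in a narrow sense. The rates said to underlie the power (12–14 points apart) are not the difference for which power is reported (10), and the printed power fits neither. On the protocol's inputs, power is 0.753 at 10 points and 0.887 to 0.959 at 12 to 14 points, against 0.66262 printed.

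These figures assume one first-pass success rate per resident, a common SD of 10 percentage points, 15 evaluable residents per arm, and the t-test rather than its rank-based alternative. The article does not show whether the slip lies in the difference entered, the SD entered, or the number transcribed. The article also leaves open which part of the learning curve the 80% describes. That needs clarifying but is not an error.

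**What to change.** In Sample size {14}:

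1. State one planning difference in absolute percentage points and restate the power for it at 15 residents per arm, with the SD given alongside.
2. If 10 points is the smallest worthwhile difference, say so. Present 80% against 92–94% only as expected rates, delete the statement that power was determined from them, and print 0.753.
3. If the software run used another difference or SD (9 points at SD 10, or 10 points at SD about 11.1, would each give 0.66262), report the value actually entered, justify it, and bring {14} and {20a} into line.
4. Say which stage of training the 80% from the department's earlier study represents, for example the mean over a stated number of first intubations.

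The cost is a few sentences and one recalculation. The design, the analysis and the number of residents do not change.

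### The stated power of 0.66262 does not follow from the stated inputs, which give 0.753; it matches a 9-point difference at SD 10, not the stated 10 points

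*Protocol article*

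**What the plan says.** The inputs to the power calculation are split between two sections of the protocol article.

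- **Sample size {14}** gives the target, "To detect a difference in means of 10", and the result, "with sample sizes of 15 in Group 1 (VL) and 15 in Group 2 (DL), the power is 0.66262", and names the software and version used.
- **Statistical methods for primary and secondary outcomes {20a}** gives the test, "The comparison will be made using a two-sided, two-sample equal-variance t-test", the error rate, "with a Type I error rate (α) of 0.05", and the variability, "The common standard deviation for both groups is assumed to be 10".

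The Sample size section also says that power was determined by "assuming an 80% first-pass success rate in the DL group [1] and 92–94% in the VL group". It then introduces the 10-point target separately: "we hypothesized that a 10% increase in the VL group compared to the DL group would constitute a significant improvement".

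The article mentions no difference of 9, no SD other than 10, no dropout allowance and no reduced group size for this calculation.

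**The concern.** Difference, SD, group size, test and error rate together determine the power of a t-test. All five are printed, so the printed power can be checked with no outside assumption. A difference equal to one SD with 15 per group should give a power of about three quarters, and the article reports about two thirds.

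This is the only statement in the article of what the trial can detect on its primary endpoint. If the result is null, readers will set it against a power and a detectable difference that do not belong together. The Discussion offers the study as a basis for later multicentre research, so anyone planning from these inputs would inherit the mismatch. Nor can a reader tell which input is misprinted: if it is the SD, the assumption stated in the methods section is wrong as well.

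**Working it through.** **Inputs**

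| Quantity | Value | Source |
|---|---|---|
| Difference in means, d | 10 | Sample size {14} |
| Residents per group, n | 15 and 15 | Sample size {14} |
| Common SD, s | 10 | Statistical methods {20a} |
| Test | two-sided, two-sample, equal-variance t | Statistical methods {20a} |
| Type I error rate | 0.05 | Statistical methods {20a} |
| Stated power | 0.66262 | Sample size {14} |

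**Formula.** Degrees of freedom are 15 + 15 − 2 = 28, and the two-sided 5% critical value is t = 2.048. The noncentrality is λ = d / (s·√(1/15 + 1/15)) = d / (s·√(2/15)). Power is P(T > 2.048) + P(T < −2.048), where T is noncentral t with 28 degrees of freedom and noncentrality λ.

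**Step 1: the plan's figure from the plan's inputs.** λ = 10 / (10 × 0.36515) = 2.739, and power = 0.75292. The stated 0.66262 is not reproduced. The gap is 0.753 − 0.663 = 0.090.

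**Step 2: which inputs do give 0.66262?** Solving with everything else held fixed:

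- For the difference at SD 10: d = 9.00001. At exactly d = 9, λ = 2.465 and power = 0.662619, which rounds to the printed value.
- For the SD at a difference of 10: s = 11.111, which gives the same λ and power.
- For the two-sided error rate at d = 10 and s = 10: 0.0278.

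With n and the error rate as stated, the printed power therefore fixes only the standardised effect, at d/s = 0.9. The printed inputs have d/s = 1.0.

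**Step 3: could another reading explain the figure?** At d = 10 and SD 10:

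| Variant | Power |
|---|---|
| Two-sided t-test, normal approximation | 0.782 |
| One-sided t-test, 0.05 | 0.848 |
| Two-sided t-test, 0.025 | 0.646 |
| Welch test (simulated) | 0.755 |
| Mann-Whitney (simulated) | 0.720 |
| Mann-Whitney, relative efficiency 3/π | 0.732 |
| Mann-Whitney, minimum relative efficiency 0.864 | 0.685 |
| 14 per group | 0.721 |
| 13 per group | 0.687 |

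A comparison of two proportions, 80% against 90%, with 15 per arm gives 0.114. Some unequal splits come close, for example 11 against 14 (0.6618), but they contradict the stated 15 and 15 and do not match to five decimals. An error rate near 0.028 contradicts the stated 0.05.

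**Step 4: how far the result moves with the inputs** (n = 15 + 15, two-sided 0.05)

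| Difference | SD | Power |
|---|---|---|
| 9 | 10 | 0.663 |
| 10 | 10 | 0.753 |
| 12 (92 − 80) | 10 | 0.887 |
| 14 (94 − 80) | 10 | 0.959 |
| 10 | 8 | 0.910 |
| 10 | 12 | 0.596 |

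The SD values of 8 and 12 are illustrative; the article gives only 10.

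**The case against.** The strongest reply concedes the arithmetic and disputes its weight. The Sample size section says that organisation and feasibility also shaped the size of the study, and the Discussion says that few residents start each year, so 30 residents was not solved from the power figure. Correcting the figure changes no enrolment, test or estimand, and no interim analysis depends on it. If 10 points and SD 10 are what was meant, the printed power errs on the cautious side. Both 0.66 and 0.75 fall short of the conventional 0.80, which would need 17 per group (0.807). A null result should in any case be read mainly from its confidence interval.

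All of that is fair, and it limits the consequence to what the article reports. It does not make the printed figure right.

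Two further points stand in part:

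- **The cause is an inference.** A difference of 9 entered in the software is the simplest explanation, because it is a whole number and the article states SD 10. An SD of 11.11 fits equally well numerically. For the same reason, 0.753 is the right power only if the printed difference and SD are the intended ones.
- **Powering on 10 when 12 to 14 is expected can be sound.** Choosing a worthwhile difference smaller than the expected one is legitimate. The fault here is one of explanation: the text presents the 80% and 92–94% rates as the basis of the power and then computes on a different difference without linking the two.

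A table of power over a range of SDs is good practice, but its absence is not an error.

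**Conclusion.** The concern holds. The difference, SD, group size, test and error rate printed in the article give a power of 0.753, not 0.66262, a misstatement of 9 percentage points. The printed value is the power for a standardised effect of 0.9: 9 points at SD 10, or 10 points at SD 11.11. No statement in the article reconciles the two.

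This rests only on the article's own inputs and the exact noncentral-t distribution. It takes as given that resident-level success rates are analysed by the equal-variance t-test, as the article states. Which input was misprinted cannot be settled from the article. The unexplained step from 12–14 points to 10 is a secondary matter of clarity. The power figure should be corrected because it is the trial's only statement of power and is wrong for the inputs given.

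**What to change.** Check the software record, rerun the calculation and print one matching set in the Sample size section, whichever was intended:

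- difference 10, SD 10, 15 per group, power 0.75; or
- difference 9, SD 10, 15 per group, power 0.66; or
- difference 10, SD 11.1, 15 per group, power 0.66, with the SD in the statistical methods section changed to agree.

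Add a sentence saying why the target is smaller than the 12 to 14 points implied by 80% against 92–94%. Preferably also give a short table of power over a range of SDs such as 8 to 12: at a difference of 10 this runs from 0.910 down to 0.596, so the SD assumption matters more than the misprint.

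The cost is one corrected sentence, one added sentence and the optional table. Enrolment, conduct and the planned analysis stay as they are.
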